### 2.7. Other Assessments

All the clinical and demographic data of patients, as well as the health care services provided by ANT physicians and nurses, will be collected on an electronic record form exploiting Cloud technology created by Vitaever SaaS (Nethical S.r.l., Bologna, Italy) (https://www.vitaever.com/) (accessed on 15 December 2022).

Data related to patients entering the study will be extracted by the Vitaever database in Excel format. The following data will be used in the study:Demographic data (sex, age).Primary site of disease (recorded according the International Classification of Diseases (9th revision) [34] and then classified as gastrointestinal, respiratory tract, genitourinary, breast, nervous system, haematological, and other), time since diagnosis, and presence of metastases. Disease stage (radically operated cancer (adjuvant therapy—supportive therapy); advanced cancer (early palliative care—supportive therapy); locally advanced cancer (adjuvant therapy); advanced cancer (palliative care only).KPS.Edmonton Symptom Assessment Scale (ESAS) [35].Cancer therapy (chemotherapy, hormone therapy, radiotherapy, immunotherapy) and pain therapy.

### 2.8. Training and Monitoring

In order to standardize the process among the physicians participating as investigators, the questionnaires and the study procedures were practiced and discussed during a training session with the Research Department staff prior to the start of the recruitment period. Moreover, the investigators were trained by the VST technicians in the use of the ButterfLife device and in the consultation of the physiological parameter reports.

Periodic meetings between the investigators and the Research Department staff have been scheduled to monitor the progress of the study and discuss the difficulties encountered.

### 2.9. Sample Size

Based on data from patients entering care in 2020, it is planned to propose the study to approximately 60 patients meeting the inclusion and exclusion criteria. Among these, it is supposed that at least 50 patients will agree to enter the study and be randomized into two groups (ButterfLife and Control) of 25 patients each.

The power of the study, calculated using the G*Power software with a post hoc power analysis for a Mann–Whitney test between two groups counting on an effect size = 0.8 and α = 0.05, was (1 − β) = 0.86. Therefore, 50 patients cared for at home by the ANT Foundation in Bologna and its province will be included in the study.

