### 2.6. Measures and Outcomes

The primary outcome of the study is the acceptability and the feasibility of the telemonitoring intervention measured as the percentage of eligible patients proposed for the study who agree to participate and the number of self-measurements/week per patient. Moreover, a questionnaire for evaluating the ButterfLife device (ease of use, difficulties encountered, and usefulness) was constructed based on several questionnaires already found in the literature [26] and will be administered to patients belonging to the ButterfLife group at the end of the telemonitoring period.

The secondary outcomes involving patients and caregivers are listed below.

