### 2.10. Statistical Analysis

A statistical analysis will be conducted on the data after their anonymization. An investigator is in charge of anonymization and blinding to groups’ patient allocation. The anonymized and blinded data will be passed to the investigators in charge of data analysis. Anonymized data will be stored within the Research Department of the ANT Foundation in an ad hoc safe electronic database. The statistical analysis will be structured as follows:Descriptive analysis of the characteristics of the recruited subjects. The following parameters are shown as frequencies: age, sex, KPS, diagnosis, time since diagnosis, presence of metastases, symptoms, current therapies, and stage of the disease.Analysis of acceptability and feasibility: percentage of eligible patients proposed for the study who agree to participate, percentage of drop out from the study, number of measurements/week per patient, patient assessment of ease of use, difficulties encountered, and usefulness.The trend of secondary outcomes (QOL, psychological state, and caregiver care burden) over time (day 1, day 28 and day 56) will be analyzed using a general linear model for repeated measures.Comparison between the ButterfLife and Control groups: after analyzing the normality of the variables (Shapiro–Wilk test), the differences between the two groups for secondary outcomes (QOL, psychological state, caregiver care burden, caregiver satisfaction with the care received, number of scheduled visits, unscheduled visits, on-call visits, phone calls received by the doctor and nurse, number of visits to the emergency room, number of hospital admissions and hospitalization) will be analyzed with parametric (Student’s *t*-test) or non-parametric tests (Mann–Whitney test).

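### The stated power of 0.86 is matched only by a one-sided calculation; for the non-directional secondary comparisons that are planned, two-sided power under the same assumptions is about 0.77

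*Protocol article*

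**What the plan says.** Section 2.9 of the protocol article first arrives at 50 patients from expected accrual: about 60 eligible patients approached, at least 50 agreeing, "randomized into two groups (ButterfLife and Control) of 25 patients each". Next comes the power statement, attributed to a post hoc run in G*Power, which reads "a Mann–Whitney test between two groups counting on an effect size = 0.8 and α = 0.05, was (1 − β) = 0.86". The section closes by drawing the inclusion of 50 patients as a conclusion from this. Sidedness, the parent distribution and the outcome to which the power applies are not given.

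Section 2.10 says that "the differences between the two groups for secondary outcomes" will be analysed with Student's *t*-test or the Mann–Whitney test, depending on normality. No direction is attached. The same section lists "percentage of drop out from the study" among the feasibility results, without an expected rate.

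Section 2.6 states: "The primary outcome of the study is the acceptability and the feasibility of the telemonitoring intervention". It is measured by the percentage of approached eligible patients who agree to take part and by the weekly number of self-measurements per patient.

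**The concern.** A reader who sees α = 0.05 beside a comparison of differences will take the test as two-sided. On that reading 0.86 is too high for 25 per group and an effect size of 0.8. The practical consequence lies in how null results are read. With power 0.86, the chance of missing a true standardised difference of 0.8 is 1 − 0.86 = 14%. With power 0.77 it is 23%. A non-significant result for quality of life, psychological status, caregiver burden or service use would look more reassuring than it should.

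The figure is also presented as the power of the study, although it cannot concern the primary outcome. Consent is recorded before randomisation and device measurements exist only in the ButterfLife group, so a two-group Mann–Whitney test applies to neither. Finally, the number randomised is the same as the number used for power, so every patient is taken to be evaluable over eight weeks.

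**Working it through.** **Inputs (Sections 2.9 and 2.10).** n = 25 per group, 1:1; standardised effect d = 0.8; α = 0.05; Mann–Whitney test; stated power 0.86. Sidedness and parent distribution are not stated.

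**Method.** Asymptotic relative efficiency (ARE) approach for the Mann–Whitney test. The sample size is multiplied by the ARE and the power is read from a noncentral *t* distribution:

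- df = 2n·ARE − 2
- noncentrality = d·√(n·ARE/2)
- ARE = 3/π = 0.955 for a normal parent

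**Numbers in.** n·ARE = 25 × 0.955 = 23.87; df = 2 × 23.87 − 2 = 45.7; noncentrality = 0.8 × √(23.87/2) = 2.76.

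**The plan's own figure.** One-sided, the critical value is *t* = 1.679 and the power is 0.859. This matches 0.86.

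**The same inputs, two-sided.** The critical value is *t* = 2.013 and the power is 0.772.

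**Simulation.** 20,000 Mann–Whitney tests on normal data gave 0.860 one-sided and 0.765 two-sided.

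**Could another setting give 0.86?** Power with 25 per group, d = 0.8:

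| Setting | One-sided | Two-sided |
|---|---|---|
| Normal parent (ARE 3/π) | 0.859 | 0.772 |
| Plain *t*-test (ARE 1) | 0.874 | 0.792 |
| Minimum ARE (0.864) | 0.827 | 0.728 |
| Logistic parent (ARE π²/9) | 0.900 | 0.828 |
| Laplace parent (ARE 1.5) | 0.963 | 0.928 |
| Normal approximation (z) | 0.882 | 0.807 |

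Only the one-sided calculation with a normal parent rounds to 0.86. No two-sided value comes within two points of it.

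**What two-sided 0.86 would take (normal parent).** At least 0.86 needs 32 evaluable per group (power 0.868) or, with 25 per group, d of about 0.90. Two-sided power of at least 0.80 needs 27 per group (0.804).

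**Loss to follow-up.** The document gives no rate, so the losses below are assumptions. Normal parent, two-sided, d = 0.8:

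| Assumed loss | Evaluable per group | Power |
|---|---|---|
| 0% | 25 | 0.77 |
| 10% | 22.5 | 0.73 |
| 20% | 20 | 0.67 |
| 30% | 17.5 | 0.61 |

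With 20 per group even the one-sided power is 0.78.

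**The case against.** The strongest reply is that nothing was miscalculated. The value 0.86 follows from the stated sample size, effect, α and test once a one-sided test and a normal parent are assumed. That is right, and the fault is therefore an unstated one-sided calculation beside a non-directional analysis, not a slip in arithmetic. It is also right that one-sidedness is inferred from the match, and that 0.77 depends on the normal parent: the two-sided variants run from 0.73 to 0.93. None of them, however, gives 0.86.

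Several stronger readings are tempting, and the document does not support them:

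- **That the trial will test one-sidedly and so overlook harm**, such as more anxiety or caregiver burden. Section 2.10 compares differences without a direction. At most the planning figure was one-sided.
- **That the plan expects substantial drop-out and real power is 0.67 or less.** Section 2.10 only lists drop-out as a result to report. Moreover, Section 2.7 draws the services provided by physicians and nurses from the electronic record, so missing questionnaires need not mean missing data for every secondary outcome.
- **That the sample size stands or falls with this figure.** Section 2.9 derives 50 from accrual before it turns to power, and calls the power analysis post hoc. The closing inference is loose, but the number has another basis.
- **That this is a critical flaw.** In a pilot whose primary outcome is acceptability and feasibility, an error confined to secondary comparisons leaves the main aim untouched.

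**Conclusion.** The power statement in Section 2.9 is wrong as written: 0.86 is not the power of the comparisons that Section 2.10 describes. For a two-sided Mann–Whitney test at α = 0.05 with d = 0.8, a normal parent and all 25 patients per group evaluable, the power is about 0.77, some 9 percentage points lower. The conclusion rests on reading Section 2.10 as two-sided, which is the natural reading of non-directional comparisons where one-sided testing is nowhere declared. The exact value of 0.77 rests on the normal parent. Severity is minor to moderate, because the consequence is limited to how null secondary results are interpreted.

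**What to change.** Keep N = 50. In Section 2.9, replace the power statement with wording such as: *For the secondary between-group comparisons, with 25 evaluable patients per group, two-sided α = 0.05, a standardised effect of 0.8 and a normal parent distribution, the power of the Mann–Whitney test is about 0.77.*

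Optionally add, marked as an assumption because no drop-out rate is given, that power falls to about 0.73, 0.67 and 0.61 with 10%, 20% and 30% loss. Calling these comparisons exploratory and reporting them with 95% confidence intervals would be sensible. So would a precision statement for the primary outcome: 50 of 60 agreeing is 83%, with a Wilson 95% interval of 72–91%. These are additions and are not needed to correct the error.

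The cost is wording only. No patients, data or analyses change; the published power becomes less favourable.

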### 2.10. Statistical Analysis

A statistical analysis will be conducted on the data after their anonymization. An investigator is in charge of anonymization and blinding to groups’ patient allocation. The anonymized and blinded data will be passed to the investigators in charge of data analysis. Anonymized data will be stored within the Research Department of the ANT Foundation in an ad hoc safe electronic database. The statistical analysis will be structured as follows:Descriptive analysis of the characteristics of the recruited subjects. The following parameters are shown as frequencies: age, sex, KPS, diagnosis, time since diagnosis, presence of metastases, symptoms, current therapies, and stage of the disease.Analysis of acceptability and feasibility: percentage of eligible patients proposed for the study who agree to participate, percentage of drop out from the study, number of measurements/week per patient, patient assessment of ease of use, difficulties encountered, and usefulness.The trend of secondary outcomes (QOL, psychological state, and caregiver care burden) over time (day 1, day 28 and day 56) will be analyzed using a general linear model for repeated measures.Comparison between the ButterfLife and Control groups: after analyzing the normality of the variables (Shapiro–Wilk test), the differences between the two groups for secondary outcomes (QOL, psychological state, caregiver care burden, caregiver satisfaction with the care received, number of scheduled visits, unscheduled visits, on-call visits, phone calls received by the doctor and nurse, number of visits to the emergency room, number of hospital admissions and hospitalization) will be analyzed with parametric (Student’s *t*-test) or non-parametric tests (Mann–Whitney test).

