The quality of life (QOL) of patients will be assessed by the EuroQoL-5D-3L questionnaire (EQ-5D-3L), Italian version [27,28], a generic instrument consisting of 2 distinct sections: patient’s subjective assessment of five dimensions of quality of life (mobility, self-care, daily activities, pain/discomfort, and anxiety/depression); each item has responses graded from 1 to 3, where level 1 indicates no problems and level 3 indicates extreme limitation. Assessment of the patient’s perceived health status will be made on a visual analogue scale (VAS) graded from 0 (the worst possible health status) to 100 (the best possible health status).The psychological status of the patient will be evaluated by the Depression Anxiety Stress Scales-21 (DASS-21), Italian version [29,30], a self-assessment scale to detect depression, anxiety and stress. The scale consists of 21 items, 7 for each emotional state, assessed on a 4-point Likert scale (from 0 = never to 3 = always).Care burden perceived by the caregiver will be assessed by the Caregiver Burden Inventory (CBI) [31], a questionnaire consisting of 24 questions on 5 domains (time-dependent care burden, developmental burden, physical burden, social burden, and emotional burden). Completion requires ticking the box from 0 to 4 (0 = not at all, 1 = slightly, 2 = moderately, 3 = quite a lot, 4 = very much) that best describes the current condition or personal impression of the caregiver. The total score ranges from 0 to 100, where 100 indicates the highest perceived caregiver burden.Satisfaction with care stated by the caregiver will be assessed through the Family Satisfaction with Advanced Cancer Care-2 questionnaire (FAMCARE-2), Italian version [32,33], a specific validated instrument to measure family members’ satisfaction with the care received from a palliative care team for their relative with advanced cancer. The FAMCARE-2 consists of 17 questions whose answers, on a 5-point ordinal score ranging from 1 (very dissatisfied) to 5 (very satisfied), cover 5 domains (management of symptoms and patient comfort, information provided, support to the family, and psychological assistance to the patient). The total FAMCARE-2 score can range from 17 to 85, where 85 represents the highest satisfaction with the care received.

The total monitoring time will be 8 weeks: at day 1, after 4 weeks (day 28), and 8 weeks (day 56), the administration of questionnaires to the patient and caregiver will be repeated (Table 2).

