Several studies regarding telemedicine in advanced cancer patients have regularly assessed psychosocial constructs and QOL [7]. Thus, previous studies and reviews reported a significantly higher QOL in telemedicine and telemonitoring interventions rather than in standard care [37,38]. Patients may receive significant support and comfort if their physicians provide them with timely and ongoing feedback on their health. One reason for the improvement of QOL is the capacity of telemedicine to reduce the geographical barrier between patients and clinical staff [38]. Moreover, the constant and continuous monitoring of vital parameters at every stage of the disease or whenever required could reduce suffering and anxiety, improving QOL. However, in this field, it is difficult to have a clear vision [7], whereas many tools could be included within telehealth and information technology (e.g., mobile phone devices, internet-based interventions, interactive health communication applications, virtual programs of support, and symptom monitoring tools) [8]. Specifically, our feasibility study may help to figure out if this telemonitoring tool is useful for advanced cancer patients assisted at home in order to increase the knowledge about the more appropriate telehealth intervention for this specific group of patients. A previous study suggested that the attention provided by telemedicine to patients with advanced cancer is helpful for maintaining quality home care [39]. In addition to reducing the impact of distance, we expect our practice could foster continuous healthcare delivery and closer communication among physicians, patients and families.

As the disease progresses, clinical condition changes and rapidly worsens; thus, adjustments and orientations are necessary to provide good care [39,40]. The daily and constant monitoring of patients’ vital parameters, albeit remotely, may enable the physician to have a clear and updated overview of the clinical trajectory of the disease and its symptoms. On the other hand, the patient may have the feeling of being constantly supported and assisted, significantly lowering distress and anxiety factors and increasing QOL. Indeed, using telemedicine, patients with significant symptoms of distress may receive a high-quality assessment and management of suffering from the comfort of their home without being compelled to move [41].

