**Figure 2 jcm-12-01922-f002:**
[figure not shown]
ButterfLife medical device.

**Table 1 jcm-12-01922-t001:** Inclusion and exclusion criteria for eligible participants.

Inclusion Criteria
Men and women with solid and hematologic malignancies in an advanced stage, i.e., a locally advanced or metastatic cancer disease that is unlikely to be cured or controlled with treatment.
Aged ≥ 18 years.
Able to understand the objectives of the study and sign the informed consent.
Able to speak and understand the Italian language.
Karnofsky Performance Status (KPS) ≥ 50.
Presence of at least one of the following comorbidities: ⋅ Chronic obstructive pulmonary disease (COPD); ⋅ Chronic ischaemic heart disease (CIC) after acute myocardial infarction (AMI); ⋅ Pulmonary emphysema; ⋅ Valvulopathy; ⋅ Systemic arterial hypertension; ⋅ Severe coronary artery disease; ⋅ Respiratory failure related to primary or metastatic lung cancer disease; ⋅ Cardiomyopathy developed after oncological treatment. This symptomatology may be directly related to the oncological disease or independent of it (pre-existing pathology at the time of cancer diagnosis, symptoms occurring as a result of oncological therapies, or age-related onset). The severity of these comorbidities must be relevant to the patient’s clinical profile as expressed in at least one of the following conditions: ⋅ Resting oxygen saturation level <90% in room air or oxygen therapy; ⋅ Systolic/diastolic blood pressure greater than 140/90 mmHg or less than 90/60 mmHg, or on antihypertensive medication; ⋅ Resting heart rate greater than 100 or less than 60 beats per minute or being treated with anti-arrhythmic drugs or the presence of a pacemaker.

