**Exclusion criteria**
Patients with a diagnosis of dementia or cognitive impairment hampering the comprehension of the study information and/or signing of informed consent.
End-of-life patients.
Patients refusing to participate.

**Table 2 jcm-12-01922-t002:** Questionnaires during the eight weeks of monitoring time. Supplementary Document 2 includes all the questionnaires administrated to patients and caregivers by the physician on Day 1, Day 28 and Day 56.

Timeline	Day 1	Day 28	Day 56
Patient	EQ-5D-3L DASS-21	EQ-5D-3L DASS-21	EQ-5D-3L DASS-21 Evaluation of the ButterfLife device *
Caregiver	CBI	CBI	CBI FAMCARE-2

EQ-5D-3L: EuroQoL-5D-3L questionnaire; DASS-21: Depression Anxiety Stress Scales-21; CBI: Caregiver Burden Inventory; FAMCARE-2: Family Satisfaction with Advanced Cancer Care-2; * Only for patients in ButterfLife group.

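### The repeated-measures general linear model for quality of life, psychological state and caregiver burden in its standard form drops anyone missing a visit and has no stated group-by-visit term; a mixed model on all available scores is the better choice

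*Protocol article*

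**What the plan says.** Section 2.10 plans two separate analyses of these scores.

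- **Time:** for quality of life, psychological state and the burden on caregivers, the trend "over time (day 1, day 28 and day 56) will be analyzed using a general linear model for repeated measures". No group term and no group-by-visit term is mentioned.
- **Groups:** after a Shapiro–Wilk check, the ButterfLife and Control groups are compared by Student's t-test or Mann–Whitney test on the secondary outcomes, which include these three.

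The schedule in section 2.6 is that "at day 1, after 4 weeks (day 28), and 8 weeks (day 56), the administration of questionnaires to the patient and caregiver will be repeated".

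On who may be lost:

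- Table 1 admits patients with "a locally advanced or metastatic cancer disease that is unlikely to be cured or controlled with treatment" and "Karnofsky Performance Status (KPS) ≥ 50".
- Table 1 excludes "End-of-life patients", a criterion applied at entry.
- Section 2.10 lists "percentage of drop out from the study" among the feasibility results, without an expected rate.
- Section 3 remarks: "As the disease progresses, clinical condition changes and rapidly worsens".
- Section 2.4 enrols patient and caregiver as a dyad.

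The article does not say how a person with a missing visit enters the model.

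**The concern.** The general linear model for repeated measures (repeated-measures ANOVA or MANOVA) takes one row per subject and needs all visits in the row. Someone who answers on Day 1 and Day 28 but not on Day 56 contributes nothing. That follows from the method the article names; it is not a detail left open.

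If those lost are on the whole the sicker ones, the fitted visit means describe completers and not the enrolled group. With 25 patients per arm, throwing away partial records is also costly. Caregivers answer the burden questionnaire themselves, so there the selection works through the dyad leaving the study.

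Because the model is described only as a trend over time, the one longitudinal analysis does not use the randomisation. The group comparison falls to single-visit tests, and a Day 56 test again rests on those still answering, without using their earlier scores.

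**Working it through.** The plan gives no figure on this point to reproduce. All attrition rates, standard deviations, correlations and loss mechanisms below are assumptions.

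**1. How many remain complete.** From section 2.9: 50 patients, 25 per arm. With loss q per four-week interval, the complete share is (1 − q)².

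| q | Complete | Of 50 | Day 1 only (50q) | Days 1 and 28 only (50(1 − q)q) |
|---|---|---|---|---|
| 10% | 0.81 | 40.5 | 5 | 4.5 |
| 20% | 0.64 | 32 | 10 | 8 |
| 30% | 0.49 | 24.5 | 15 | 10.5 |

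At 20%, the discarded assessments per questionnaire are 10 × 1 + 8 × 2 = 26, out of 26 + 32 × 3 = 122 collected.

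As a weekly rate, (1 − w)⁸ for w = 2%, 3% and 5% gives 0.85, 0.78 and 0.66, so 21 to 17 of 25 per arm for the two extremes.

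**2. Level and change on a 0–100 score.** Assumed: true means 55, 50 and 45, SD 20, correlation 0.6 between all visits, 68% complete, log-odds of loss rising 0.7 to 1.0 per SD of worse score. The simulation was large, so the differences are bias and not noise; a repeat run agreed to within 0.1 point. The true change is 45 − 55 = −10.0.

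| Loss depends on | Estimate | Day 56 mean (true 45.0) | Change (true −10.0) |
|---|---|---|---|
| Last observed score | Completers | 47.7 to 48.6 | −10.9 to −11.2 |
| Last observed score | Likelihood, all visits | 45.0 | −10.0 |
| Current, unseen score | Completers | 48.6 to 49.8 | −9.1 to −8.8 |
| Current, unseen score | Likelihood, all visits | 46.9 to 47.6 | −8.1 to −7.4 |

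In the first row completers also start higher: 47.7 + 10.9 = 58.6 at the lower end, against a true 55. That is why the level is off by about 3 points and the change by only about 1.

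**3. A second setting, in SD units.** Assumed: true change −0.50, correlation 0.7 between adjacent visits, loss 10% to 30% per interval, log-odds 0.7 to 1.1 per SD.

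- Loss on the last observed score: completers' change −0.54 to −0.62, their Day 56 mean −0.42 to −0.19; the likelihood estimate recovers −0.50.
- Loss on the current unseen score: completers' change −0.47 to −0.36, their Day 56 mean −0.39 to −0.06.
- Loss unrelated to the score: no bias, but records are still discarded.

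Whenever loss follows health, completers look better at Day 56 than the enrolled group. The error in the change has no fixed sign.

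**The case against.** **The article nowhere says that only complete cases are analysed.** True. It is a property of the named method in its standard form, and an analysis plan that is not shown could add imputation or another model. It would then have to replace or supplement the method published here. Handling of missing visits may be left to that plan; the point concerns the model that is named.

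**Loss may be modest.** The performance-status criterion and the end-of-life exclusion both limit loss over eight weeks. The planned drop-out percentage is a feasibility result, not a forecast, and the remark on rapid worsening is general discussion. This stands: the size cannot be fixed from the document.

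**The model is meant for the trend, and the trend is little affected.** This also stands. A reader might infer that decline will look too flat because fitter patients remain. The simulations do not support that as a rule: when loss follows the last observed score, completers show slightly more decline.

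**A false group difference?** A reader might infer one from this model. The model as described contains no group term, so it cannot produce it. The separate group test could, if loss differed by arm: with an assumed 77% v 56% complete and no true effect, completers differed by 2.0 points at Day 56. Nothing in the document points to unequal loss. With 25 × 0.77 ≈ 19 and 25 × 0.56 = 14 completers and SD 20, the standard error is 20 × √(1/19 + 1/14) = 7.0, so this is 0.28 standard errors.

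**A mixed model does not cure survivor bias.** Correct. The exact recovery of 45.0 follows from simulating loss that is missing-at-random. When loss depended on the unseen score, the likelihood change was further from the truth than the completers' change, though its Day 56 mean was closer. Scores after death are a question of definition that no such model settles.

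**Conclusion.** The point holds in limited form. The named model, in its standard form, discards partial records and estimates completers' levels, and as described it makes no use of the randomisation. A mixed model on all available visits is the better default for these three outcomes.

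The size is unknown because no attrition rate is given. Under the assumptions shown, the Day 56 level is off by roughly 3 to 5 points on a 0–100 score and the change by about 1 point in either direction. The advantage of the mixed model is shown only for loss that depends on observed scores. The document does not support a claim that the planned trend is biased in a known direction, or that the replacement resolves death or loss driven by unseen scores.

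This should be changed, but it touches only secondary outcomes of a 50-patient pilot. The acceptability and feasibility outcome is unaffected.

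**What to change.** In section 2.10, replace the general linear model with a linear mixed model for repeated measures:

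- Fit it by REML to all available Day 1, Day 28 and Day 56 scores for quality of life, psychological state and caregiver burden, with visit, group and group-by-visit terms.
- Take the group contrasts for these three outcomes at Day 28 and Day 56 from this model. Caregiver satisfaction, collected once at Day 56, and the service-use counts can keep their planned tests.
- State that the model is valid only under missing-at-random, and that it does not resolve truncation by death or loss that depends on unseen scores.
- Report deaths and withdrawals by arm beside the results.
- Add a simple sensitivity analysis for loss not at random, for example shifting the missing scores downwards over a stated range.

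The cost is slightly more analysis work in standard software and an assumption that must be stated. No new data are needed. The article's data availability statement says recruitment is in progress, so the change can be made before analysis.
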